### Randomisation

The randomisation will be done using the on-line randomisation tool (Randomizer.at) which is self-serve and runs exclusively on the Internet. An on-screen form with patient details will be completed. The treatment allocation will be immediately notified. The randomisation will be performed regarding treatment arms A and B. Stratification parameters include the following criteria: age (< 30, ≥ 30 years) and gender.

As this is an open-label study there will be no blinding of treatment assignment.

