## Organization, Workflow and Follow-up

Patient data will be collected and documented pseudonymously using electronic data processing (e.g. patient initials, date of birth and study number) at the study office at HIT. Table 3 presents a brief workflow.

**Table 3 T3:** Workflow time table

Approval of ethics committee
↓
Diagnosis of chordoma of the skull base and completion of pre-radiation treatment examinations (biopsy, operation, staging)
↓
Informed consent of the patient and patient registration by the study office at HIT
↓
Stratification and Randomisation
↓
Arm A: carbon ion RT (63 Gy E ± 5%, fractionation 4-6 × 3.0 Gy E) Arm B: proton RT (72 Gy E ± 5%, fractionation 4-6 × 2.0 Gy E)
↓
Treatment planning for particle therapy
↓
Particle therapy
↓
Follow-up

After randomisation the study number will be assigned.

The following study data will be collected at the study office at HIT:

1. Medical reports including pathology reports and results of staging and additional pre-treatment examinations

2. Documentation of RT (dose distributions and DVH) and position checks

3. Prescribed total target dose and fraction doses, treatment interruptions >4 days

4. Toxicity data

5. Follow-up forms

6. Trial-related documentation including severe AE (CTCAE Grad ≥ 3) will be reported immediately to the study office and the principal investigator of the study

7. The date of local recurrence (MRT or CT - morphological tumour progress in the former irradiated region), distant metastases or death of the patient will be reported and documented.

Local recurrences will be confirmed radiologically and histologically whenever possible. At least two medical doctors (radiation oncologist and/or radiologist) will be required to judge of the recurrence or toxicity.

Every patient is followed for LPFS and trial-related AEs for a time period of 8 years. Furthermore, patients will be followed for survival and locoregional recurrences for a time period of 8 years after completion of the irradiation.

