The first and the second follow-up examination will be performed 4-6 weeks and 3 months after completion of RT (follow-up 1 and 2). Follow-up examinations will then be scheduled after 6 months (follow-up 3), 9-12 months (follow-up 4), and then once a year for further 6 years (follow-up 5, 6 and 7). Additional visits will be scheduled as necessary. Acute toxicity is assessed at least weekly during RT and documented at the end of the RT series, 6 weeks after completion of RT and 3 months after RT. Late toxicity will be documented in regular intervals of 6 or 12 months during the observation period. All the patients will be observed for radiation specific acute and late AEs for the time of at least 8 years after irradiation. The maximum grade of toxicity will be determined for each patient.

The Common Terminology Criteria for Adverse Events V4.0 (CTCAE V.4.0) will be used to grade acute toxicity from radiation therapy. The criteria are relevant from the 8th irradiation day until day 90, i.e. until the 1st follow-up visit. Thereafter, the RTOG/EORTC Criteria of Late Effects will be utilized. All acute radiation effects will be documented on an Acute Radiation Effect-Form. In addition, the AE-Form and/or SAE-Form will be filled out. RTOG/EORTC Late Morbidity Scoring Scheme will be used to grade toxicity from radiation therapy occurring later than 90 days after its start, i.e. beyond the 1st follow-up visit. All late radiation effects will be documented on a Late Radiation Effect-Form. In addition, an AE-Form and/or SAE-Form will be filled out, if late radiation effects appear.

The follow-up examinations contain:

- Medical history

- Clinical examination

- MRI or CT of the head

- Documentation of acute side effects/AE (CTCAE V.4.0) up to 90 days after RT

- Documentation of late side effects/AE (RTOG/EORTC) after 90 days after RT

- Reporting/documentation of acute grade 3 or 4 toxicity or grade 3, 4 or 5 late effects.

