### Study duration and interruption criteria

Accrual period for the trial will be approximately 5 years starting on autumn 2010. The study ends with the enrollment of planned 344 patients. Our study design contains interim analysis after observation period of 7 years. Definite assessments of LPFS, survival and for radiation specific AEs will be possible approximately 8 years after completion of radiation therapy of the last recruited patient.

The individual reasons for the study interruption are the patient dead or the withdrawing agreement of the patient to participate in the study.

With proven recurrence of disease or the development of distant metastases, the patient will be censored for our study and will be eligible for any additional appropriate therapy or inclusion in other investigative protocols, but should still be followed in order to document survival and radiation specific AEs.

The study can be early terminated under following considerations:

- high incidence of unknown AEs or increase in known AEs with the disadvantageous proportion between risk and benefits of the proposed radiation therapy;

- unacceptable high rates of SAEs;

- other reasons challenging the ethical basis;

- official decision.

All subjects who have adverse events, whether considered associated with the therapy, must be monitored to determine the outcome. The clinical course of the adverse event will be followed up according to accepted standards of medical practice, even after the end of the period of observation, until a satisfactory explanation is found or the investigator considers it medically justifiable to terminate follow-up. Should the adverse event result in death, a full pathologist's report should be supplied, if possible.

Each adverse event occurring in connection with the therapy has to be documented, independent of the cause.

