### Safety Analysis

The safety analysis will be based on the safety population. The assessment of safety will be based mainly on the frequency of adverse events or serious adverse events the acute and late toxicities and on the number of laboratory values that fall outside of pre-determined ranges and/or show prominent worsening. Furthermore, the most common AEs (those occurring in at least 10% of the treatment group) will be determined. Any other information collected (e.g. severity or relatedness to study drug) will be listed as appropriate. Incidence rates and exact Pearson-Clopper 95% confidence bounds [27] of AE will be summarized.

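### The scope of adverse event capture is stated inconsistently, narrow in some sentences and broad in others; under the narrow reading, attribution by doctors who know the arm would decide which late events are recorded

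*Protocol article*

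**What the plan says.** All references are to the protocol article.

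**Narrow wordings**
- Organization, Workflow and Follow-up sets the long-term scope by relatedness: "Every patient is followed for LPFS and trial-related AEs for a time period of 8 years".
- The same section then sets it by type of event: "All the patients will be observed for radiation specific acute and late AEs for the time of at least 8 years after irradiation".
- The same section ties the late-phase form to a late radiation effect: "In addition, an AE-Form and/or SAE-Form will be filled out, if late radiation effects appear".
- Study duration and interruption criteria repeats the radiation-specific restriction twice: for the final assessment about 8 years after the last patient's treatment, and for patients still followed after recurrence or metastasis.

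**Broad wordings**
- Organization, Workflow and Follow-up has CTCAE grade 3 or higher events reported at once to the study office. The visit list covers side effects and AEs without stating a relatedness condition.
- Study duration and interruption criteria says: "All subjects who have adverse events, whether considered associated with the therapy, must be monitored to determine the outcome".
- Safety Analysis rests mainly on the frequency of AEs and serious AEs, with acute and late toxicities and laboratory values. Relatedness is only an attribute: "Any other information collected (e.g. severity or relatedness to study drug) will be listed as appropriate".

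**Mixed wording**
- Study duration and interruption criteria also says: "Each adverse event occurring in connection with the therapy has to be documented, independent of the cause". The sentence limits itself to events connected with the therapy and then disclaims cause.

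**Context**
- Randomisation states: "As this is an open-label study there will be no blinding of treatment assignment". At least two doctors judge toxicity, but they are not said to be masked.
- The early-termination criteria include "high incidence of unknown AEs or increase in known AEs" and, as a separate item, unacceptably high rates of serious AEs.

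**The concern.** A site working from these sentences cannot tell whether a late event thought to be unrelated goes on a form. The wordings on each side lead to different databases.

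The late period is the most exposed. After 90 days grading moves to the RTOG/EORTC late scheme, and the AE or serious AE form is triggered by a late radiation effect. If relatedness is the condition for entry, doctors who know the arm decide which events exist for analysis. Toxicity is named as a secondary endpoint in the Abstract and morbidity is listed among the secondary objectives. The arms differ in particle, total dose and dose per fraction, so the comparison of late toxicity matters. Any difference between arms in the readiness to attribute would pass straight into that comparison.

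A harm not yet recognised as caused by particle therapy is also the kind of event that the narrow wording is most likely to miss, and one termination criterion looks for such harms.

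A statistical analysis plan could not repair this afterwards, because it can only analyse what was recorded.

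**Working it through.** The point rests on the text, and the plan gives no figure to reproduce. The arithmetic in step 4 is an illustration on assumed inputs.

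**Step 1: compare the sections.** Take a grade 2 late event judged unrelated, in a patient without recurrence.
- Under the 8-year sentence in Organization, Workflow and Follow-up it falls outside follow-up, because it is not trial-related.
- Under the late-form sentence there it triggers no form, because it is not a late radiation effect.
- Under the monitoring sentence in Study duration and interruption criteria it must be followed to its outcome. The words 'or not' appear to be missing from that sentence, but no other reading makes sense of it.
- Under Safety Analysis it would count in the AE frequency, with relatedness listed beside it. A relatedness field carries little information if only related events are collected.

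These cannot all be followed.

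**Step 2: compare sentences within Study duration and interruption criteria.** The monitoring sentence is broad. The documentation sentence is mixed. The post-recurrence and final-assessment sentences are narrow. Aligning the follow-up section to this one would therefore not settle the matter, because this section contradicts itself.

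**Step 3: what is captured under any reading.** Severe AEs (CTCAE grade 3 or higher) are reported immediately. No explicit relatedness condition is placed on the AE itself, although the list item opens by referring to trial-related documentation. So the narrow wording does not clearly remove all unrelated events.

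**Step 4: illustration of what attribution could do.**
- Input from the protocol: 344 patients with equal allocation, so 344 / 2 = 172 per arm.
- Assumed, not in the documents: the same true incidence r in both arms, with only events judged related recorded, with probability a in one arm and b in the other.
- Recorded rates are r × a and r × b, so the apparent risk ratio is a / b whatever r is.
 - Equal attribution: ratio 1.0, no bias.
 - 80% against 70%: 0.8 / 0.7 = 1.14.
 - 80% against 60%: 0.8 / 0.6 = 1.33.
 - 90% against 60%: 0.9 / 0.6 = 1.5.
- Chance of a nominal two-sided p < 0.05 if the arms were tested, for 80% against 60% and r = 20%: recorded rates 0.16 and 0.12; SE = √[(0.16 × 0.84 + 0.12 × 0.88) / 172] = √(0.24 / 172) = 0.0374; z = 0.04 / 0.0374 = 1.07; chance about 19%. With r = 10% it is about 11%, and with r = 30% about 28%.
- Safety Analysis plans incidence rates with exact 95% bounds and specifies no such test. These chances describe how misleading the summary could look. They are not an error rate of the plan.

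**The case against.** **The narrow sentences may not be capture rules.** The 8-year sentence mainly sets a duration. The radiation-specific wording may mean the kind of toxicity scored on a late-effects scale, not a causal verdict case by case. Immediate grade 3 or higher reporting and the visit items state no relatedness condition. This stands in part: it is too much to say that capture is limited to related events. It does not remove the conflict, because the relatedness wording in the 8-year sentence and the late-form trigger remain.

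**Attribution need not decide what is compared.** Safety Analysis applies no relatedness filter, and nothing in the documents suggests that attribution differs by arm or in which direction. This stands. The bias is conditional on the narrow wording governing and on unequal attribution.

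**The termination criterion.** A reader might infer that the criterion on unknown AEs cannot work because such events would never be collected. The documents do not support that. Unknown is not defined and, set against known AEs, plausibly means not previously described, so such an event can still be judged therapy-related and recorded. Severe events are reported immediately, and the serious AE rate is a separate criterion. At most the criterion is weakened under the narrowest reading.

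**A journal article condenses.** Detailed reporting rules commonly sit in the full protocol, and their absence here is no finding. The point concerns sentences that are present and disagree.

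**Conclusion.** The inconsistency is real and can be read directly from the text. AE scope differs between Organization, Workflow and Follow-up, Study duration and interruption criteria, and Safety Analysis, and also within the second of these. The consequence is conditional. If the narrow wording governs, unmasked attribution filters late events, and the apparent risk ratio becomes the ratio of the attribution probabilities: 1.14 to 1.5 over the unequal pairs assumed above, and 1.0 if attribution is equal. The size in this trial cannot be derived from the documents.

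This is a cheap improvement worth making before late events accumulate. It does not show that the toxicity comparison is biased.

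**What to change.** 1. State one scope in Organization, Workflow and Follow-up and in Study duration and interruption criteria, including the sentences on follow-up after recurrence or metastasis and on the final assessment: all serious AEs and all AEs of grade 3 or higher are recorded for the whole observation period regardless of attribution, with attribution as a separate field.
2. Remove the internal conflict in the documentation sentence, and complete the monitoring sentence so that it plainly covers events whether or not they are attributed to therapy.
3. Name the scale for late events outside the RTOG/EORTC late-effects scheme. CTCAE is the natural choice, since the protocol already uses it to define severe AEs.
4. In Safety Analysis, summarise all-cause incidence by arm first and attributed events second.

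The cost is wording in three sections and some additional AE forms at visits that already take place. All-cause rates carry more background events, so the contrast between arms is slightly noisier. The change takes attribution out of the recording decision for these events. It does not remove open-label bias in detecting or grading them.

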### Study duration and interruption criteria

Accrual period for the trial will be approximately 5 years starting on autumn 2010. The study ends with the enrollment of planned 344 patients. Our study design contains interim analysis after observation period of 7 years. Definite assessments of LPFS, survival and for radiation specific AEs will be possible approximately 8 years after completion of radiation therapy of the last recruited patient.

The individual reasons for the study interruption are the patient dead or the withdrawing agreement of the patient to participate in the study.

With proven recurrence of disease or the development of distant metastases, the patient will be censored for our study and will be eligible for any additional appropriate therapy or inclusion in other investigative protocols, but should still be followed in order to document survival and radiation specific AEs.

The study can be early terminated under following considerations:

- high incidence of unknown AEs or increase in known AEs with the disadvantageous proportion between risk and benefits of the proposed radiation therapy;

- unacceptable high rates of SAEs;

- other reasons challenging the ethical basis;

- official decision.

All subjects who have adverse events, whether considered associated with the therapy, must be monitored to determine the outcome. The clinical course of the adverse event will be followed up according to accepted standards of medical practice, even after the end of the period of observation, until a satisfactory explanation is found or the investigator considers it medically justifiable to terminate follow-up. Should the adverse event result in death, a full pathologist's report should be supplied, if possible.

Each adverse event occurring in connection with the therapy has to be documented, independent of the cause.

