## Methods and Design

### Primary objectives/endpoints of the study

The primary objective of this study is to evaluate, if the innovative therapy (carbon ion irradiation) in chordomas is superior to the standard proton treatment with respect to the Local-progression free survival (LPFS) defined as time from the randomisation to observed local recurrence or death from any cause in the absence of documented local disease progression. Local recurrence defined as MRT or CT - morphological tumour progress in the former irradiated region. A 10% increase in the LPFS is considered clinically relevant assuming that the LPFS rate for the proton therapy is 70%.

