### Analysis Populations and General Considerations

Analysis populations will be defined as follows:

The ITT population will include all patients who are randomised, with radiation therapy administration designated according to initial randomisation, regardless of whether patients receive study treatment or receive a different treatment from that to which they were randomised. This will be the primary population for evaluating all efficacy endpoints as well as subject characteristics.

The safety population consists of all subjects who received at least one dose of irradiation administration designated according to actual study treatment received.

The PP population will consist of all subjects of the ITT population who completed the particle therapy, have at least 2 post-baseline assessments regarding the primary endpoint without pre-specified (in the statistical analysis plan), selected major protocol deviations thought to impact on efficacy analysis.

The statistical analysis will be done as soon as the database has been declared to be complete and accurate and has been locked. The details of the analysis will be laid out in the statistical analysis plan, which will be finalized and approved prior to the database lock. It has to be authorized before by the biometrician and the principle investigator. Missing values will not be replaced or imputed. For patients with incomplete follow-up, time to last follow-up date will be used as the censoring time in the analysis of time-to-event data.

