### Efficacy Analysis

#### Primary efficacy analysis

LPFS is defined as the time from date of randomisation to local recurrence or death from any cause in the absence of documented local disease progression. LPFS will be censored on the date of the last tumour assessment on study for patients who do not have local tumour progression and who do not die while on study.

A log-rank test (two-sided) will be used to compare LPFS between the two treatments. The LPFS-rates will be derived from the Kaplan Meier estimate [22] and the confidence intervals will be calculated using Greenwood's formula.

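### The instruction to censor patients at recurrence or distant metastasis contradicts the LPFS definition; at metastasis it would lose primary-endpoint events informatively

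*Protocol article*

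**What the plan says.** All references are to the protocol article.

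- *Primary objectives/endpoints of the study*: LPFS is "defined as time from the randomisation to observed local recurrence or death from any cause in the absence of documented local disease progression".
- *Primary efficacy analysis*: the event is the same ("LPFS is defined as the time from date of randomisation to local recurrence or death from any cause"). Censoring is confined to patients with neither event: "LPFS will be censored on the date of the last tumour assessment on study for patients who do not have local tumour progression". Deaths on study are likewise kept out of the censored group. Distant metastasis is not mentioned.
- *Organization, Workflow and Follow-up*: "Every patient is followed for LPFS and trial-related AEs for a time period of 8 years". The same section adds survival and locoregional recurrence follow-up for 8 years after irradiation, with no stop at metastasis.
- *Study duration and interruption criteria*: "With proven recurrence of disease or the development of distant metastases, the patient will be censored for our study". The sentence then opens other therapy and other protocols to the patient, "but should still be followed in order to document survival and radiation specific AEs". Local tumour status is not on that list.

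**The concern.** A patient who develops distant metastases and later recurs locally, or dies without local progression, is an LPFS event under the endpoint and efficacy sections. Under the interruption section the same patient is a censored observation. No sentence says which section governs or exempts LPFS from the censoring instruction.

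Two things are at stake.

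1. **Analysis.** Kaplan-Meier and the log-rank test need censoring that is independent of the event. Patients with metastases are plausibly at higher risk of death, which is itself an LPFS event. Censoring them at metastasis removes people just as their hazard rises, so the LPFS curves come out too high. It also departs from the intention-to-treat analysis named as primary.
2. **Data collection.** If sites follow the shorter list and stop local assessment after metastasis, later local recurrences are never recorded. A statistical analysis plan finalised before database lock cannot recover them.

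The sentence also sits badly with the secondary endpoints PFS and metastasis-free survival, whose names imply that recurrence or metastasis is the event.

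**Working it through.** **Inputs from *Sample Size Determination* and *Interim Analysis*.** 5-year LPFS of 70% (proton) and 80% (carbon), two-sided 0.05, power 0.80, 1:1 allocation, 5-year accrual, 13 years maximum observation, 143 events, 319 patients before and 344 after 7% loss, interim critical value 2.9626.

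**Step 1: reproduce the plan.**
- λ₁ = −ln(0.70)/5 = 0.0713; λ₂ = −ln(0.80)/5 = 0.0446; hazard ratio 1.598, log 0.469.
- Schoenfeld: 4(1.960 + 0.842)²/0.469² = 142.7, so 143 events.
- With uniform accrual, follow-up t runs from 8 to 13 years. The mean of 1 − exp(−λt) is 0.525 and 0.373, average 0.4487. 143/0.4487 = 318.7, so 319 patients; 319/0.93 = 343.01, so 344.
- The two-stage O'Brien-Fleming-type design gives an interim z of 2.9626, a final z of about 1.969, and power 0.799 at 143 events.

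The sample size holds, and it matches LPFS as the efficacy section defines it, with no censoring at metastasis.

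**Step 2: apply censoring at metastasis, with local recurrence still counted.** The documents give neither a metastasis rate nor the risk after metastasis, so both are assumed, equal in the two arms: metastasis hazard m = 0.005 to 0.02 per year, and LPFS-event hazard after metastasis g = 0.2 to 0.4 per year. Before metastasis the planned λ applies.

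- Events kept per patient: λ/(λ+m) × mean of [1 − exp(−(λ+m)t)].
- True LPFS: S(t) = exp(−(λ+m)t) + m/(g−λ−m) × [exp(−(λ+m)t) − exp(−gt)]. True events per patient: mean of 1 − S(t).
- Both are averaged over the arms and multiplied by 319. Power is for the two-stage design at hazard ratio 1.598, using the events kept.

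| m | g | True events | Kept | Lost | Power |
|---|---|---|---|---|---|
| 0.005 | 0.2 | 147.5 | 139.8 | 5.2% | 79% |
| 0.005 | 0.4 | 149.7 | 139.8 | 6.6% | 79% |
| 0.02 | 0.2 | 159.5 | 130.4 | 18.2% | 76% |
| 0.02 | 0.4 | 167.6 | 130.4 | 22.2% | 76% |

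For example, at m = 0.02 the kept probabilities are 0.479 and 0.339, so 319 × (0.479 + 0.339)/2 ≈ 130; lost share = (167.6 − 130.4)/167.6 = 22.2%.

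**Step 3: effect on the reported rates.** Under this censoring, Kaplan-Meier estimates 0.700 and 0.800 at 5 years. The true values S(5) run from 0.695 to 0.666 (proton) and from 0.794 to 0.759 (carbon) across the table. The overstatement is therefore about 0.5 to 3.4 points and 0.6 to 4.1 points respectively.

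**Step 4: simpler cross-check.** If metastasis is treated as independent of LPFS, a 5-year metastasis incidence of 2%, 5% or 10% leaves about 140, 136 or 130 events and power of about 79%, 78% or 76%.

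**The case against.** The sentence stands in a section on interruption and termination, beside wording about other therapy and other trials. It can be read as loose language for a patient going off protocol. The efficacy section is the place that specifies the primary analysis, and it does so correctly. The follow-up section keeps every patient under LPFS observation and records dates of local recurrence, metastases and death. Deaths after metastasis stay available even under the interruption section.

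Much of this stands. It disposes of the stronger inference that local recurrences themselves would be censored, leaving only deaths without recurrence as events. If such deaths were 10–50% of LPFS events (an assumption), about 14–72 events would remain and power would be about 14–51%. But that reading would abolish the primary endpoint, contradicts both statements of the LPFS definition, and does not fit the sample size. It is a literal worst case.

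The objection does not cure the metastasis conflict. The efficacy and follow-up sections imply that such patients stay at risk and under local assessment. The interruption section says they are censored, and omits local status from what is collected afterwards.

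A reader might also see a conflict of censoring dates, since *Analysis Populations and General Considerations* says "For patients with incomplete follow-up, time to last follow-up date will be used as the censoring time" while the efficacy section says "LPFS will be censored on the date of the last tumour assessment on study". That is a general rule beside a specific one. The specific rule ordinarily governs, and every scheduled follow-up examination includes head imaging, so the dates will mostly coincide. It is not part of this point.

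**Conclusion.** The contradiction is real and concerns the primary endpoint. Its firm part is distant metastasis: following the interruption section would censor plausibly informatively, drop later local recurrences and deaths, and overstate LPFS in both arms.

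Under the assumed hazards, 5–22% of true LPFS events are lost, about 130–140 remain from 319 patients against the 143 planned, and power at the planned hazard ratio is about 76–79%. A reader might apply the lost share to 143 and infer a larger power loss. That is not supported: the share is taken from the true events, which exceed 143 in this model (up to 167.6) because events after metastasis come on top of the planned hazards.

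The size rests entirely on the assumed metastasis and post-metastasis hazards. The documents do not allow the direction of any bias between arms to be derived, and none is claimed. The sample size itself is not in error.

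**What to change.** Replace the word for censoring in *Study duration and interruption criteria* with wording that says:

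1. local recurrence is an LPFS event at its date;
2. distant metastasis, new therapy or entry into another protocol does not censor LPFS in the primary intention-to-treat analysis;
3. the local tumour assessment and survival follow-up already set out in *Organization, Workflow and Follow-up* continue after metastasis.

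Censoring at the start of new therapy may be kept as a labelled sensitivity analysis.

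The cost is a wording change and no additional patients. The one practical burden is continued routine head imaging in the few patients with metastases, which the follow-up schedule already plans.
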